## **9 STUDY POPULATION**

### **9.1 Eligibility Criteria**

#### **9.1.1 Inclusion Criteria**

To receive randomized treatment assignment, participants must fulfill the following inclusion criteria at the Screening Visit and prior to the initiation of study treatment, unless another time is specified:

1. Participant is  $\geq 18$  years of age;
2. Participant has a confirmed diagnosis of PsA per the 2006 CASPAR with symptoms for  $\geq 6$  months prior to the Screening Visit (see [Appendix 1](#) in Section 21.1);

*Note:* New X-ray images of hands and/or feet are not required. Results of the most recent X-ray images of hands and/or feet will be captured in the eCRF. If no previous images exist, X-rays may be obtained as part of routine management at the discretion of the investigator.

3. Participant has active disease (defined by a TJC68 of  $\geq 3$  and a SJC66 of  $\geq 3$ );
4. Participant has either current active PsO or a dermatologist confirmed history of PsO;
5. Participant tests negative for rheumatoid factor (RF) at the Screening Visit;
6. Participant tests negative for anti-cyclic citrullinated peptide (CCP) antibodies at the Screening Visit;
7. Participant must be, in the opinion of the investigator, a suitable candidate for treatment with adalimumab per approved local product information. If a chest X-ray or computerized tomography (CT) scan for TB screening is required per local guidance, the X-ray or CT scan must be taken within 3 months prior to the Screening Visit;
8. Participant has had an inadequate response at the Screening Visit (lack of efficacy after  $\geq 12$ -week duration of therapy) to previous or current treatment with  $\geq 1$  non-biologic DMARD at maximally tolerated dose, or participant has an intolerance to or contraindication for DMARDs as defined by the investigator;
9. If the participant is female, she must be of non-childbearing potential or, if of childbearing potential, participant must agree to use highly effective methods of contraception. See [Appendix 2](#) in Section 21.2 for the definition of non-childbearing potential, childbearing potential, and highly effective methods of contraception;
10. Women of childbearing potential (as defined in [Appendix 2](#) in Section 21.2) must have a negative serum human chorionic gonadotropin (hCG) pregnancy test at the Screening Visit and a negative urine pregnancy test at Week 0/Day 1 prior to the first administration of study treatment;

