### **4.2 Secondary Efficacy Endpoints**

The key secondary efficacy endpoints of this study are:

- ACR20 response rate at Week 12 compared with baseline;
- Psoriasis Area and Severity Index (PASI) 90 at Week 12 compared with baseline in the subgroup of participants with psoriasis (PsO) involving at least 3% body surface area (BSA) at baseline.

The other secondary endpoints this study are:

- Response rate compared with baseline at specified timepoints other than Week 12 for the following:
  - ACR20;
  - ACR50
  - PASI90.
- Response rate compared with baseline at specified timepoints for the following
  - ACR70;
  - Minimal disease activity at Week 12, defined as meeting 5 of the 7 following criteria:
    - Tender joint count (TJC)  $68 \leq 1$ ;
    - Swollen joint count (SJC)  $66 \leq 1$ ;
    - PASI  $\leq 1$  or PsO affecting  $\leq 1\%$  of BSA;
    - Patient's Assessment of Arthritis Pain (PtAAP)  $\leq 15$  on a 0 to 100 visual analog scale (VAS);
    - Patient's Global Assessment of Disease Activity (PtGADA)  $\leq 20$  on a 0 to 100 VAS;
    - Health Assessment Questionnaire Disability Index (HAQ-DI)  $\leq 0.5$ ;
    - Leeds Enthesitis Index (LEI)  $\leq 1$ .
  - PASI75 at specified timepoints compared with baseline (in the subgroup of participants with PsO involving at least 3% BSA at baseline);
  - PASI100 at specified timepoints compared with baseline (in the subgroup of participants with PsO involving at least 3% BSA at baseline);

- Response rate of at least 50% improvement compared with baseline in the Bath Ankylosing Spondylitis Disease Activity Index (BASDAI);

[figure not shown]

- The change from baseline at specified timepoints for the following:
  - TJC68;
  - SJC66;
  - Enthesitis evaluation (LEI and Spondyloarthritis Research Consortium of Canada [SPARCC] enthesitis index);
  - Leeds Dactylitis Index (LDI);
  - Modified Nail Psoriasis Severity Index (mNAPSI);
  - High sensitivity C-reactive protein (hs-CRP);
  - PtGADA;
  - Physician's Global Assessment of Disease Activity (PhGADA);
  - Psoriatic Arthritis Impact of Disease (PsAID)-12;
  - PtAAP;
  - HAQ-DI;
  - Functional Assessment of Chronic Illness Therapy for Fatigue (FACIT-Fatigue);
  - Short-Form-36 Health Survey Questionnaire-Version 2 (SF-36v2) Mental Component Summary (MCS);
  - SF-36v2 Physical Component Summary (PCS);
  - BASDAI;

[figure not shown][figure not shown]

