| Endpoint                                           | 
The key secondary endpoints are as follows:
 
 
• ACR20 response rate at Week 12 compared with baseline;
 
• PASI90 at Week 12 compared with baseline in the subgroup of participants with PsO involving at least 3% BSA at baseline.
 
                                                                                                                                                                                                                                                                                                                                                                                                                                                                                                                           |
| Population-level summary                           | 
The primary estimator will be the improvement compared to placebo over the 12-week based on the endpoint of interest.
                                                                                                                                                                                                                                                                                                                                                                                                                                                                                                                                                                                                                                                                                                |

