#### **6.1.3 Full Analysis Set (FAS)**

The FAS is defined as all randomized participants. Participants will be analyzed in accordance with the intention-to-treat (ITT) principle, i.e., based on randomized treatment, irrespective of the treatment they actually received.

The FAS will be used for all efficacy analyses on efficacy endpoints related to the Part A and some Part A+B analyses and will serve as the primary analysis set.

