### **8.6.3.2 Psoriasis Area and Severity Index 90**

A key secondary endpoint is change from baseline in PASI90 at Week 12 in the subgroup of participants with psoriasis [PsO] involving at least 3% body surface area [BSA] at baseline. This is expected to be between 50% and 67% of the FAS.

The PASI is a validated tool to dynamically assess PsA severity.

The PASI score is an established measure of clinical efficacy for PsO medications, which provides a numeric scoring for the participant's overall PsO disease state, ranging from 0 to 72. It is a linear combination of percent of surface area of skin that is affected and the severity of erythema, infiltration and desquamation over 4 body regions (Head, Trunk, Upper extremities, Lower extremities).

These correspond to 10%, 30%, 20% and 40% of the total body area respectively.

The area of psoriatic involvement of these 4 areas (Ah, At, Au, and Al) is given a numerical value:

- 0 = No involvement;
- 1 = <10%;
- 2 = 10% to <30%;
- 3 = 30% to <50%;
- 4 = 50% to <70%;
- 5 = 70% to <90%;
- 6 = 90% to 100% involvement.

The signs of severity, erythema (E), infiltration (I), and desquamation (D) of lesions are assessed using a numeric scale 0 to 4 where 0 is a complete lack of cutaneous involvement and 4 is the

severest possible involvement; scores are made independently for each of the areas, h, t, u and l and represent a composite score for each area.

An illustration of judging erythema follows:

- 0 = No erythema;
- 1 = Slight erythema;
- 2 = Moderate erythema;
- 3 = Striking erythema;
- 4 = Exceptionally striking erythema.

The PASI score is calculated according to the following formula:

$$\text{PASI} = 0.1(\text{Eh} + \text{Ih} + \text{Dh})\text{Ah} + 0.3(\text{Et} + \text{It} + \text{Dt})\text{At} + 0.2(\text{Eu} + \text{Iu} + \text{Du})\text{Au} + 0.4(\text{El} + \text{Il} + \text{Dl})\text{Al}$$

PASI90 is defined as an improvement of 90% or more in the PASI from baseline score.

The PASI90 will be assessed at Baseline, Week 4, Week 8, Week 12, Week 16, Week 20 and Week 24, but the key secondary endpoint is the assessment at Week 12.

The null hypotheses to be tested are that the proportion of PASI90 responders at Week 12 are not different for the following comparisons:

- sonelokimab 120 mg Q2W versus placebo
- sonelokimab 60 mg Q2W versus placebo
- sonelokimab 60 mg Q4W versus placebo

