## 8.6.4 Analysis of Other Secondary Efficacy Endpoints

For the other secondary endpoints, no confirmatory statistical testing will be performed, but statistical analyses may be used for exploratory proposes.

FAS will be used for all other secondary endpoints analysis. Summaries of part B will be performed using the FAS-B population.

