### 8.6.4.15 ACR and PASI Composite Endpoints

4 composite endpoints will be created combining ACR and PASI endpoints:

- ACR50 and PASI90
- ACR50 and PASI100
- ACR70 and PASI90
- ACR70 and PASI100.

A subject is considered a responder for the composite endpoints at a particular timepoint if they are a responder for both of the relevant endpoints at that same timepoint. If either is missing or non-responder then the subject will be considered a non-responder.

To test these hypotheses, a pairwise stratified logistic regression will be used as detailed in [Section 8.6.1.1](#). Descriptive summaries by treatment group and visit will also be displayed for Part A and Part B combined for NRI/LOCF.

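### The ACR+PASI composites have no baseline BSA restriction and count a missing PASI response as failure, so an unknown share of participants cannot respond

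*Combined protocol and SAP*

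**What the plan says.** - **Composite rule (SAP 8.6.4.15).** A participant responds only by meeting both the ACR and the PASI criterion at the same timepoint. On missing data: "If either is missing or non-responder then the subject will be considered a non-responder". The section names neither an analysis set nor a BSA threshold.
- **Analysis set (SAP 8.6.4, the parent section).** "FAS will be used for all other secondary endpoints analysis". SAP 6.1.3: "The FAS is defined as all randomized participants".
- **Stand-alone PASI endpoints.** The key secondary in SAP 5.3 is "PASI90 at Week 12 compared with baseline in the subgroup of participants with PsO involving at least 3% BSA at baseline". SAP 4.2 limits PASI75 and PASI100 in the same way. On the size of that subgroup, SAP 8.6.3.2 says "This is expected to be between 50% and 67% of the FAS".
- **Entry (Protocol 9.1.1, criterion 4).** "Participant has either current active PsO or a dermatologist confirmed history of PsO".
- **PASI derivation (SAP 8.6.3.2).** PASI90 is a reduction of 90% or more from the baseline score. Protocol Table 1 schedules PASI with no BSA condition.
- **Status.** SAP section 9 lists the composites as an addition to the protocol. SAP 8.6.4 makes testing of other secondary endpoints exploratory, and the procedure in SAP 8.6.1.4 does not include them.

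**The concern.** The BSA condition attached to the stand-alone PASI endpoints is not written down when PASI is combined with ACR. A percentage improvement from a baseline of zero is undefined, so a participant who enters with psoriasis by history and clear skin has no PASI response. Under the missing-data rule that participant is a treatment failure in all four composites, whatever happens in the joints.

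This differs from the plan's practice elsewhere. LEI and SPARCC (SAP 8.6.4.6), LDI (8.6.4.9) and mNAPSI (8.6.4.11) are analysed in participants with a baseline score above zero, and baseline PASI is summarised only where BSA is at least 3% (8.4.2). Minimal disease activity (8.6.4.4) counts PASI of 1 or less as meeting its skin criterion, so the same clear-skinned participant passes there and fails here.

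The composite rate then depends partly on how many participants had enough psoriasis at entry, as well as on the drug. The SAP also does not say how PASI response is set for participants with BSA below 3% and PASI above 0, so two programmers could follow the text and report different rates.

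**Working it through.** **The plan's own power figure.** The documents give no rate or power for the composites. Their only power statement is for ACR50 (SAP 5.5: 40 per arm, 10% vs 40%, 2-sided alpha 0.025, power above 80%). Pooled two-proportion formula, no continuity correction:

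- null SE = sqrt(2 × 0.25 × 0.75 / 40) = 0.0968
- alternative SE = sqrt((0.10 × 0.90 + 0.40 × 0.60) / 40) = 0.0908
- power = Φ((0.30 − 2.241 × 0.0968) / 0.0908) = 82.0%

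The stated figure reproduces, and the same formula is used below at 2-sided alpha 0.05 (SAP 8.1).

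**Forced-failure share.** Let f be the share of the FAS with baseline BSA of at least 3% (0.50 to 0.67, SAP 8.6.3.2). Let g be the share of the remainder who cannot have a PASI response. The documents do not give g, so it is varied. Share = (1 − f) × g.

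| g (assumed) | f = 0.67 | f = 0.50 |
|---|---|---|
| 0.25 | 8% | 13% |
| 0.50 | 17% | 25% |
| 1.00 | 33% | 50% |

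The last row applies if PASI response is treated as defined only in the BSA subgroup, or if everyone outside it has PASI 0. It is 13 to 20 of 40 per arm, or 66 to 100 of 200.

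**Effect at the upper bound (g = 1).** FAS rate = f × subgroup rate. The rate therefore cannot exceed f (50-67%), and the risk difference is f times the subgroup risk difference. Response rates are assumptions. The subgroup has 20 per arm (f = 0.50) or 27 per arm (f = 0.67); the FAS has 40.

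| Placebo vs active in subgroup | Subgroup difference (points) | FAS difference, f = 0.50 / 0.67 | Power, subgroup → FAS, f = 0.50 | Power, subgroup → FAS, f = 0.67 |
|---|---|---|---|---|
| 2% vs 20% | 18.0 | 9.0 / 12.1 | 44.2% → 42.1% | 56.4% → 54.3% |
| 2% vs 30% | 28.0 | 14.0 / 18.8 | 68.9% → 64.1% | 82.0% → 78.5% |
| 5% vs 30% | 25.0 | 12.5 / 16.8 | 55.1% → 50.8% | 68.6% → 64.9% |
| 5% vs 40% | 35.0 | 17.5 / 23.5 | 77.7% → 70.5% | 89.1% → 84.8% |
| 5% vs 50% | 45.0 | 22.5 / 30.2 | 92.2% → 84.6% | 97.8% → 95.0% |

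Power falls by about 2 to 8 points. It falls little because the FAS analysis keeps 40 per arm; what suffers is the size of the reported effect. For g below 1, the dilution also depends on response among participants with BSA below 3% and PASI above 0, which the documents do not give.

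**The case against.** **FAS does not by itself mean that no BSA limit applies.** Protocol 12.3.3.1 restricts PASI90 to the subgroup and also assigns it to the FAS, and SAP 8.6.4.3 omits the limit because SAP 4.2 carries it. The composites might be meant to inherit the subgroup. Part of the SAP 4.2 list is not shown, so a restriction there cannot be excluded. This stands as a caution. It does not settle the matter, because a PASI endpoint that is missing outside its subgroup becomes, under the rule in 8.6.4.15, a non-response and not an exclusion.

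**Not everyone outside the subgroup is shown to fail.** A reader might infer that 33-50% of participants are automatic non-responders. The documents do not support that as a fact. PASI is collected on everyone and PASI90 is derived from the score alone, so a participant with BSA below 3% and PASI above 0 has a calculable response. The 33-50% is an upper bound.

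**Chance imbalance is not bias.** BSA is not a stratification factor, and at 40 per arm the subgroup share can differ between two arms by 1.96 × sqrt(2 × 0.5 × 0.5 / 40) = 22 points (95% range). A reader might take this as bias in the comparison. It is random variation, and the effect on the composite is the share difference times the subgroup rate. With no drug effect, 67% vs 50% at a common rate of 30-40% gives 0.17 × 0.30 = 5 to 0.17 × 0.40 = 7 points.

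**Joint response among all randomised participants is a legitimate question.** True, but the plan does not use that population for its key PASI endpoint, and counting clear skin as a skin failure does not answer it well.

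**Conclusion.** The point holds in limited form. As written, participants with baseline PASI 0 cannot be composite responders, and the text leaves open whether all others with BSA below 3% fail too. The share affected is unknown: at most 33-50% of the FAS, or about 8-25% if a quarter to a half of those outside the subgroup have PASI 0. The cap of 50-67%, the halving to two-thirding of the risk difference and the 2-8 point power loss belong to the upper bound. They rest on the plan's expected subgroup size; the power figures also rest on assumed response rates and an unadjusted test in place of the planned logistic regression.

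The consequence is limited. The composites are exploratory, lie outside the type I error procedure and feed no decision rule. The primary and key secondary conclusions are untouched. This is a cheap improvement to how four supporting endpoints are read.

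**What to change.** In SAP 8.6.4.15, state that all four composites are analysed in participants with baseline BSA of at least 3%, as for PASI90, and that non-responder imputation applies within that subgroup. This also removes the baseline PASI 0 problem in practice, since measurable skin involvement is then required. Baseline PASI should not be added as a covariate: SAP 8.6.1.1 adds a baseline score only when the endpoint has a single score, which a composite does not.

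The cost is one sentence and smaller denominators, about 20 to 27 participants per arm in place of 40, and the result then describes patients with measurable psoriasis only. The choice should be fixed before Part A is unblinded, because choosing the denominator later would be data-driven.

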## 8.7 Pharmacokinetic and Immunological Analyses

For PK and IG Analyses, no confirmatory statistical testing will be performed, but statistical tests may be used for exploratory proposes only. IG and PK analysis sets will be used.

### 8.7.1 Immunological Analyses

Antibodies to sonelokimab will be evaluated in serum samples collected for Arms 1, 2, & 3 (120 mg Q2W, 60 mg Q2W and 60 mg Q4W sonelokimab) at Baseline, Week 2, Week 4, Week 8, Week 12, Week 14, Week 16, Week 20, Week 24 and the safety follow-up visit. At dosing visits, the samples will be collected prior to dose administration.

Up to three separate ADA types may be assessed: ADAs that bind to sonelokimab ('ADA'); ADA to a modified version of sonelokimab ('mADA') and ADA that neutralise the activity of sonelokimab ('NAb ADA'). Results for mADA will only be available for ADA baseline positive participants. NAb ADA results will only be available for the ADA positive samples.

Summary tables for each ADA type will be prepared to record where applicable the number and percentage of participants who are:

- ADA positive at baseline;
- ADA positive at any visit post-baseline;
- ADA positive at baseline and any visit post-baseline;
- ADA positive post-baseline but not at baseline;
- Treatment-emergent ADA defined as either:
  - ADA positive post-baseline but not at baseline, or
  - Treatment boosted: > 4-fold increase in ADA titers at any post-baseline timepoint compared to baseline, if ADA positive at baseline. [ $10^{(\text{post-baseline log10 titer} - \text{baseline log10 titer})} > 4$ ]
- persistent positive (positive at more than one post-baseline visit where the first and last ADA-positive visits are separated by a period of 12 weeks or longer; or positive at last post-baseline assessment and not at baseline; or positive at a visit with less than 12 weeks before an ADA-negative last visit);
- transient positive (positive at only 1 post-baseline visit and not at baseline; or positive at two or more visits where the first and last ADA-positive visits are separated by a period less than 16 weeks and the last visit is negative).

The log10 titer values for the ADA and mADA (not NAb ADA) will be summarised by visit and treatment arm.

Additional analyses may be performed at the sponsor's discretion but they are beyond the scope of this SAP and will be specified in a separate document, if needed.

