### **12.4 Subgroup Analyses**

Subgroup analyses for the primary endpoint and key secondary endpoints may be considered for the following baseline variables:

- Age;
- Sex;
- Geographic region;
- Race;
- Body weight;
- Exposure to biologic agents prior to the Screening Visit;
- Concomitant methotrexate at baseline;
- Concomitant non-biologic DMARD at baseline;
- Concomitant corticosteroids at baseline;
- Baseline hs-CRP;
- Treatment-emergent ADA status.

All summaries will be based on imputed data as appropriate and will include descriptive statistics.

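### Three of the five clauses that define persistent and transient ADA positivity in SAP 8.7.1 omit any baseline or titre-rise condition, so unchanged pre-existing antibodies can be counted in those rows

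*Combined protocol and SAP*

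**What the plan says.** SAP 8.7.1 lists the summary rows to be produced for each ADA type. Treatment-emergent ADA has two limbs: "ADA positive post-baseline but not at baseline, or" a boosted limb, defined as "> 4-fold increase in ADA titers at any post-baseline timepoint compared to baseline, if ADA positive at baseline". A participant with pre-existing antibodies is thus treatment-emergent only if the titre rises.

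Two further rows follow at the same list level, *persistent positive* and *transient positive*. Persistent has three alternative clauses:

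- clause 1: "positive at more than one post-baseline visit where the first and last ADA-positive visits are separated by a period of 12 weeks or longer";
- clause 2: "positive at last post-baseline assessment and not at baseline";
- clause 3: a positive visit less than 12 weeks before a last visit that is negative.

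Transient has two:

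- clause 1: a single positive post-baseline visit in someone negative at baseline;
- clause 2: two or more positive visits whose first and last are under 16 weeks apart, with a negative last visit.

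The SAP expects participants who are positive before dosing. It has rows for them and a modified assay aimed at them: "Results for mADA will only be available for ADA baseline positive participants". The immunogenicity analysis set (SAP 6.1.4) does not exclude them.

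**The concern.** The treatment-emergent row exists to separate antibody induced or boosted by sonelokimab from reactivity that was there beforehand. The persistent and transient rows apply that separation in two clauses and drop it in three. A participant whose antibodies did not change on treatment can therefore enter rows that sit directly beneath the treatment-emergent row and read as a breakdown of it.

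Immunogenicity is part of a stated secondary objective and ADA is a listed endpoint. If two participants with unchanged pre-existing ADA stay positive and nobody else develops ADA, the table shows two persistent and no treatment-emergent participants. That cannot be interpreted as a description of the immune response to the drug.

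**Working it through.** The plan states no figure to reproduce. The check applies the clauses literally.

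**Step 1: conditions by clause (SAP 8.7.1)**

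| Clause | Baseline or titre condition |
|---|---|
| Persistent 1 | none |
| Persistent 2 | negative at baseline |
| Persistent 3 | none |
| Transient 1 | negative at baseline |
| Transient 2 | none |

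**Step 2: two baseline-positive profiles, titre unchanged (fold rise 1, not above 4, so not treatment-emergent)**

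Sampling is at Weeks 2, 4, 8, 12, 14, 16, 20, 24 and follow-up (SAP 8.7.1), with follow-up at Week 30 (protocol Table 1). Spans are taken over post-baseline visits; the SAP does not say whether the baseline visit counts.

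- Positive at every visit: span 30 − 2 = 28 weeks, at least 12, so persistent by clause 1. For US participants (SAP 3.1), with follow-up taken as Week 10 + 8 = Week 18, the span is 18 − 2 = 16 weeks, with the same result.
- Positive at Weeks 2 and 4, then negative: span 2 weeks, under 16, and the last visit is negative, so transient by clause 2, although the antibody disappeared on treatment.

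**Step 3: all positive/negative patterns for a baseline-positive participant with unchanged titre**

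With k post-baseline visits there are 2^k − 1 patterns containing at least one positive. These are patterns, not patients.

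| Schedule | Patterns | Persistent | Transient | Treatment-emergent |
|---|---|---|---|---|
| Weeks 2 to 30 (k = 9) | 511 | 476 | 87 | 0 |
| US, Weeks 2 to 12 and 18 (k = 5) | 31 | 24 | 11 | 0 |
| Part A only, Weeks 2 to 12 (k = 4) | 15 | 7 | 4 | 0 |

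In a Part A-only table the always-positive participant has a span of 12 − 2 = 10 weeks and no negative last visit, so is neither persistent nor transient. The entries in the last line are participants who lose positivity within Part A.

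**Step 4: effect of restricting both rows to treatment-emergent ADA (Weeks 2 to 30)**

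For baseline-positive participants with unchanged titre, persistent falls from 476 to 0 and transient from 87 to 0. For baseline-negative participants nothing changes (480 persistent, 96 transient of 511), because anyone newly positive is already treatment-emergent.

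**Step 5: overlap of the two classes**

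A baseline-negative participant positive at Weeks 2 to 16 and then negative has a span of 14 weeks: at least 12, so persistent, and under 16 with a negative last visit, so transient. In all, 65 of the 511 baseline-negative patterns fall in both classes. Using 12 weeks in both definitions reduces this to 17. The rest arise because persistent clauses 2 and 3 can hold together with a transient clause. For example, a single positive at Week 24 followed by a negative at Week 30 meets persistent clause 3 (30 − 24 = 6 weeks) and transient clause 1.

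**Step 6: size**

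The documents give no baseline ADA rate. With about 40 per arm, each participant wrongly placed in the persistent row adds 1/40 = 2.5 percentage points. Purely as an assumption, if 5% to 30% of an arm were positive at baseline and all stayed positive at an unchanged titre, that is 0.05 × 40 = 2 to 0.30 × 40 = 12 participants.

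**The case against.** The strongest reply is that little depends on these rows. SAP 8.7 plans no confirmatory ADA testing, and the protocol plans listings and descriptive statistics. The same table reports baseline positives, positives both before and after dosing, new positives and treatment-emergent ADA separately, so a reader can see how much pre-existing reactivity there is. That stands, and it limits the importance of the point.

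The reach is also limited. In a Part A-only table the always-positive participant is not persistent. Whether a longer ADA table will be produced is not settled: SAP 6.1.4 assigns the immunogenicity set to Part A and Part A+B, while SAP 8.1 restricts Part A+B tables to adverse events. However, SAP 8.7.1 lists ADA visits to Week 24 and follow-up, so classification over that span is evidently intended.

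It could also be argued that persistent and transient were meant as subdivisions of treatment-emergent ADA. The list does not show this: the two limbs of treatment-emergent ADA are indented beneath it, and these two rows are not. Nor does the wording fit. Within a treatment-emergent subset, "or positive at last post-baseline assessment and not at baseline" would drop from clause 2 the boosted participants whom the SAP counts as treatment-emergent. If baseline-positive participants were meant to be included throughout, the two exclusions have no purpose. Neither reading makes the five clauses consistent.

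**Conclusion.** The definitions are inconsistent as written. Beyond Week 12, unchanged pre-existing ADA can be counted as persistent or transient, and the persistent count can exceed the treatment-emergent count. This is a modest point about descriptive tables for a secondary objective. Its numerical size is unknown without a baseline ADA rate; the range of 2 to 12 per arm is illustrative only.

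Four stronger readings are not supported:

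- A reader might infer that the SAP reports these participants as having a lasting antibody response to sonelokimab. The row is labelled only as persistent positivity, and drug-induced ADA has its own correctly defined row.
- A reader might infer that every ADA table is affected in the same way. The always-positive participant does not enter the persistent row in a Part A-only table.
- A reader might infer that subgroup results are affected, since protocol 12.4 lists "Treatment-emergent ADA status". That variable does not use the persistent or transient definitions, and SAP 8.10 does not include it in its subgroup list.
- A reader might suspect that the boosted rule is unclear for an exact fourfold rise. The rule requires more than fourfold, so an exact fourfold rise is not boosted; numerical rounding is a matter for programming checks.

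**What to change.** In SAP 8.7.1:

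1. Define persistent and transient only among participants who meet the SAP's treatment-emergent ADA definition, boosted participants included. This condition replaces the two existing baseline exclusions. For ADA types without titres, restrict both rows to participants negative at baseline; SAP 8.7.1 leaves neutralising ADA out of the titre summaries.
2. Use one duration cut-off in place of 12 and 16 weeks, and define transient as treatment-emergent but not persistent. The second part is needed because a common cut-off alone leaves 17 of 511 baseline-negative patterns in both classes.
3. Leave unchanged pre-existing ADA in the existing row for participants positive at baseline and at any later visit.
4. State whether the baseline visit counts towards the span between first and last positive visits, and which period the ADA table covers, so that SAP 6.1.4 and 8.1 agree.

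The cost is SAP wording and a few lines of programming. No new samples or assays are needed. Restricting to treatment-emergent ADA changes no count for baseline-negative participants; separating the two classes reassigns only those who currently fall in both or whose span lies between the two cut-offs.
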